#### Sample size {14}

The calculated sample size is based on an OIT rate of 30.2% for patients with COVID-19 who require mechanical ventilation [17]. Thus, we estimate that a total of 126 patients (63 in each group) would provide 80% of power to detect an absolute reduction of 20% of the primary result [18], with the adoption of a two-tailed model and a significance level of 0.05. Assuming a loss of follow-up of 20%, 151 patients will be recruited.

Assuming an intubation rate of 61% for patients with acute respiratory syndrome requiring mechanical ventilation [19], we calculated that a total of 194 (97 in each group) patients would provide 80% power to detect an absolute reduction 20% of the primary result [18], with the adoption of a two-tailed model and a significance level of 0.05. Assuming a loss of follow-up of 20%, 232 patients will be recruited. The sample size calculations were performed using the G*Power software (Version 3.1.9.6) [20]. A total of 383 patients will participate in the study, 151 in the group of patients with suspicion or confirmation SARS-CoV-2, and 232 for those with respiratory syndrome who require non-invasive ventilation.

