### Statistical methods

#### Statistical methods for primary and secondary outcomes {20a}

The SPSS software program (version 25.0, IBM, Armonk, NY, USA) will be used for data analysis using the Generalized Estimation Equations (GEE) model. The normality of the data will be assessed using the Kolmogorov-Smirnov test. Identity function, unstructured work correlation matrix, and covariance matrix of the robust estimator will be used using the Bonferroni post hoc test when significant. The chi-squared test will be used to compare the proportions of categorical variables studied in the groups and the Mann-Whitney *U* test to compare the distributions of continuous variables between groups (*p* < 0.05). Analysis by intention-to-treat will be performed to include patients who did not allow analysis of outcomes.

The effect size will be estimated according to Cohen [28], who suggested a cutoff value greater than or equal to 0.8 representing a large effect size, between 0.8 and 0.2 as a medium effect size, and values below 0.2 as a small effect size. The same will be calculated using the variation obtained before and after the intervention, as well as for the post-intervention moment between the groups analyzed. The effect size will be calculated using [name] Effect Size Calculator [http://www.uccs.edu/lbecker/].

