#### Methods for additional analyses (e.g., subgroup analyses) {20b}

Statistical analysis will be performed using the generalized estimating equations (GEE) model. The chi-squared test will be used to compare the proportions of categorical variables studied in the groups and the Mann-Whitney *U* test to compare the distributions of continuous variables between groups (*p* < 0.05). The effect size will be estimated according to Cohen [28]. It will be calculated using the variation obtained before and after the intervention, as well as for the post-intervention moment between the analyzed groups.

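### Grading every effect size from 0.2 to 0.8 as medium, with no interval, lets chance between-mask differences in secondary outcomes carry that word about 26% (COVID) or 16–17% (non-COVID) of the time

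*Protocol article*

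**What the plan says.** The grading rule is in the protocol article under Statistical methods for primary and secondary outcomes {20a}. It cites a published source, "who suggested a cutoff value greater than or equal to 0.8 representing a large effect size", and places the remaining values "between 0.8 and 0.2 as a medium effect size, and values below 0.2 as a small effect size". So there are three words, and the middle one spans a fourfold range.

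The same section says what the effect size is computed on: the before-to-after variation, "as well as for the post-intervention moment between the groups analyzed". Methods for additional analyses {20b} repeats this without the cut-offs: "It will be calculated using the variation obtained before and after the intervention, as well as for the post-intervention moment between the analyzed groups". Neither section puts an interval around the effect size or links the grade to a test result. Testing is described separately: a GEE model, chi-squared tests and Mann-Whitney tests at the 5% level.

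The group sizes come from Sample size {14}. For COVID patients, "we estimate that a total of 126 patients (63 in each group) would provide 80% of power". For the others, "we calculated that a total of 194 (97 in each group) patients would provide 80% power". With the allowance for loss, 151 and 232 patients are to be recruited.

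**The concern.** A verbal grade is useful only if its boundaries are wide relative to the precision of the estimate. Here the boundary between *small* and *medium* is set at 0.2, close to one standard error at the planned group sizes. Many outcomes on which the two masks do not differ will cross it by chance.

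Outcomes {12} lists many continuous secondary measures, among them PaO2/FiO2, PaCO2, comfort on a visual analogue scale and about ten ventilatory variables. If each is reported with its grade, some null or trivial differences will be described as medium. A reader shown the word without an interval cannot tell such a result from a well-estimated moderate difference.

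A second, smaller matter is the before-after effect size. The wording does not settle whether this means the change within one arm or the between-arm difference in change. Both arms receive NIV, so a within-arm change reflects NIV, concomitant care and time, and does not compare the masks.

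**Working it through.** **Inputs.** Cut-offs 0.2 and 0.8 ({20a}); 63 and 97 per arm, and 151 and 232 recruited ({14}); two-sided 5% level ({14}, {20a}). Assumption: the effect size is a standardised mean difference *d* between two equal arms.

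**Step 1: check that 63 and 97 are the evaluable sizes.** The first calculation is "based on an OIT rate of 30.2% for patients with COVID-19 who require mechanical ventilation"; the second begins "Assuming an intubation rate of 61% for patients with acute respiratory syndrome requiring mechanical ventilation". Each takes an absolute reduction of 20 points. With the pooled-variance formula for two proportions,

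n = [1.96·√(2p̄(1−p̄)) + 0.842·√(p₁q₁ + p₂q₂)]² / 0.20²

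- COVID, 30.2% v 10.2%: p̄ = 0.202, n = 62.1, rounded up to 63 per arm (power 80.6%).
- Non-COVID, 61% v 41%: p̄ = 0.51, n = 96.9, rounded up to 97 per arm (power 80.0%).

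The plan's figures reproduce. They are the sizes before the allowance for loss: 126 × 1.2 = 151.2 and 194 × 1.2 = 232.8, matching 151 and 232 when truncated. Full recruitment is therefore about 75 and 116 per arm.

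**Step 2: standard error of *d* when there is no true difference.** SE(d) ≈ √(2/n).

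- n = 63: √(2/63) = 0.178, so 0.2 is 0.2/0.178 = 1.12 SE from zero.
- n = 97: √(2/97) = 0.144, so 0.2 is 0.2/0.144 = 1.39 SE from zero.

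**Step 3: probability of the word *medium* under no difference.** P(0.2 ≤ |d| < 0.8) = 2·P(T > 0.2/SE) − 2·P(T > 0.8/SE), with T on 2n − 2 degrees of freedom. The second term is negligible (about 0.00002 at n = 63, and less at 97).

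| Per arm | Normal | t | Simulated, normal data | Simulated, lognormal data |
|---|---|---|---|---|
| 63 | 26.2% | 26.4% | 26.6% | 27.5% |
| 97 | 16.4% | 16.5% | 16.3% | 16.7% |
| about 75 | 22.1% | 22.3% | – | – |
| about 116 | 12.8% | 12.9% | – | – |

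These count both directions. Counting only differences that favour one mask halves them, to about 13% and 8% at 63 and 97.

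**Step 4: where the grade and the test disagree.** Two-sided p < 0.05 in a two-sample t comparison needs |d| of about 1.96 × 0.178 = 0.35 at 63 per arm and 1.96 × 0.144 = 0.28 at 97. Between 0.2 and those values the result is graded *medium* and is not significant. An observed *d* of exactly 0.2 has an approximate 95% CI of 0.2 ± 0.35, or −0.15 to 0.55, at 63 per arm, and 0.2 ± 0.28, or −0.08 to 0.48, at 97. The planned Mann-Whitney test has no exact threshold in *d*, but should behave similarly.

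**Step 5: effect of a different lower edge.** If *medium* began at 0.5 (a proposed value, not one in the documents), the null probability in Step 3 would be 0.6% at 63 per arm and 0.06% at 97.

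**Step 6: before-after effect sizes.** These figures do not carry over to a within-arm change. There SE ≈ √(2(1−r)/n), where r is the before-after correlation, which the documents do not give. With no change and r from 0.3 to 0.7, the chance of reaching 0.2 is about 18% down to 4% at 63 patients, and 10% down to 1% at 97.

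**The case against.** The strongest objection is that the grade is only descriptive. Inference runs through the stated tests, and nothing in the article says that conclusions follow from the grade. This stands, and it limits the point to wording. A reader might infer that a quarter of null secondary outcomes would become false-positive findings. The documents do not support that: the 5% tests are unchanged, and the primary outcome, intubation, is binary.

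A second objection is that relabelling moves the same noise from *medium* to *small*. This also stands, so the interval is the substantive part of the remedy. A full analysis plan may well contain intervals; the finding is the grading rule that the article does state.

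Third, the rates depend on which size applies. They are lower at full recruitment, and about 7% if the two strata were pooled to 63 + 97 = 160 per arm. But the article sizes the strata separately, so the stratum figures are the natural ones.

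Other stronger readings are tempting and should not be drawn:

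- Read literally, a large negative value falls below 0.2 and would be *small*. A large/medium/small scale is naturally read as magnitude, and nothing says signed values are graded.
- A near-certain false *medium* somewhere among the secondary outcomes would need independent outcomes. Several ventilatory variables are mechanically linked.
- Regression to the mean carrying a before-after effect into *medium* depends on an assumed source population. Eligibility criteria {10} also give PaO2/FiO2 ≤ 300 only as an alternative to SpO2 ≤ 94%.
- Whether the cited source is misreported cannot be checked from the documents, and nothing here depends on it.

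**Conclusion.** The point holds at minor severity. The stated rule overstates small between-arm differences. At 63 and 97 evaluable patients per arm, a continuous secondary outcome with no true difference would be called *medium* about 26% and 16–17% of the time, or about 22% and 13% if everyone recruited is evaluable. Part of the *medium* band, from 0.2 to about 0.35 or 0.28, is not significant at the planned level.

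This rests on *d* being a standardised mean difference, on strata analysed separately, and on counting both directions. It is an expected proportion per outcome, not a forecast for any one result. The before-after effect size is ambiguous: it is a problem only if meant within arm and then read as evidence about the mask.

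**What to change.** Amend the effect-size sentences in {20a} and {20b}:

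1. Report each between-arm effect size (post-intervention value, or difference in change) with its 95% CI.
2. Grade the absolute value in four bands: below 0.2 *negligible*, 0.2 to below 0.5 *small*, 0.5 to below 0.8 *medium*, 0.8 and above *large*. These cut-offs are a proposal.
3. Do not describe an effect of the mask by its grade when the interval includes zero.
4. State whether the before-after effect size is within arm or between arms. If within arm, report it ungraded and draw no conclusion about the mask from it.

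The cost is a few sentences, with no new data and no change to the tests or sample size. The downside is that some effects will carry a less favourable word.

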### Interventions

#### Explanation for the choice of comparators {6b}

The active arm is the use of the Owner mask to implement NIV, in addition to routine supportive care. The Owner mask (Owntec Soluções em Engenharia, Santa Cruz do Sul, Brazil) was chosen for evaluation because there is safety data from the pilot study which proved reduced air leakage due to its better seal on the patient’s face. The control arm is composed of patients who will undergo NIV using the traditionally used orofacial interface.

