### Outcomes {12}

#### Primary outcome measure

OTI rate in patients with or without suspicion or confirmation of SARS-CoV-2 infection submitted to NIV with Owner mask or conventional orofacial mask.

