#### Secondary outcome measure

In-hospital mortality [period: up to 30 days]Differences in the PaO_2_/FiO_2_ ratio regarding the baseline values (before NIV) [period: 48 h]Improvement in the PaO_2_/FiO_2_ ratio after beginning NIV [period: 1 h after NIV]PaCO_2_ levels [period: 1 to 12 h after NIV]Blood pressure (BP) and hypotension incidence (SBP < 80 mmHg or mean arterial pressure < 60 mmHg) [period: up to 2 h after NIV]Time between beginning NIV and its endICU time [time period: up to 30 days]Length of hospital stay of patients who used NIVAdverse events of the mask [period: obtained at pre-hospital discharge]Comfort of the patient with the mask (visual analog scale—VAS) [period: obtained at pre-hospital discharge]Satisfaction level (PGIC) after using NIV [period: obtained at pre-hospital discharge]NIV success rate with masks [deadline: 1 h since the beginning of NIV]Tidal volume (Vt), minute volume (MV), peak pressure (Ppeak), respiratory rate (RR), FiO_2_, inspiratory time (Ti), expiratory time (Te), air leak, inspiratory minute volume (VMi), and expiratory minute volume (VMe) obtained in NIV [period: 1 h after NIV]

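### One planned Cohen effect size is most naturally read as a within-arm before-after change and the other ignores the pre-NIV value, so neither is a baseline-adjusted comparison of the masks

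*Protocol article*

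**What the plan says.** Section {20a} of the protocol article grades effect sizes by fixed cut-offs. It sets "a cutoff value greater than or equal to 0.8 representing a large effect size", then "between 0.8 and 0.2 as a medium effect size, and values below 0.2 as a small effect size". It then says what is graded: "The same will be calculated using the variation obtained before and after the intervention, as well as for the post-intervention moment between the groups analyzed". Section {20b} repeats this for the additional analyses: "It will be calculated using the variation obtained before and after the intervention, as well as for the post-intervention moment between the analyzed groups".

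The quantities concerned are continuous secondary outcomes with a value before NIV, for example "Improvement in the PaO_2_/FiO_2_ ratio after beginning NIV [period: 1 h after NIV". The data collection sections also describe pre-NIV values for blood gases, vital signs and ventilatory parameters.

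Both arms are ventilated non-invasively. Section {6b} states: "The control arm is composed of patients who will undergo NIV using the traditionally used orofacial interface". The formal comparison of the arms is planned separately, by GEE, the Mann-Whitney U test and, for proportions, as follows: "The chi-squared test will be used to compare the proportions of categorical variables studied in the groups".

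**The concern.** The objectives in section {7} ask how the Owner mask compares with the orofacial mask. In the effect-size sentence, the reference to the groups attaches to the post-intervention calculation. The before-after calculation is therefore most naturally taken within one arm, with no input from the other.

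Such a number contains whatever NIV does through either mask, the effect of concomitant care, and regression to the mean in patients who enter with poor oxygenation (section {10}). A medium band that opens at 0.2 can then be reached with no difference between the masks.

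The second effect size does compare the arms, but only on post-NIV values. It leaves out a baseline that the trial already collects, and so gives up precision.

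At stake is how the size of any benefit on PaO2/FiO2, PaCO2, respiratory rate and similar outcomes is described.

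**Working it through.** **Inputs from the protocol article.** Cut-offs 0.2 and 0.8 ({20a}). From {14}: 63 per arm (COVID-19) and 97 per arm (non-COVID), two-sided 0.05, 80% power, intubation rates 30.2% and 61%, absolute reduction 20 points. The article states no mean change, SD or pre-post correlation for any continuous outcome, so these are assumed and varied below.

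**1. The plan's own figures.** n = [1.96·√(2p̄q̄) + 0.8416·√(p1q1 + p2q2)]² / δ².
- COVID-19, 0.302 v 0.102: (1.96·√0.3224 + 0.8416·√0.3024)² / 0.04 = 62.1, giving 63.
- Non-COVID, 0.61 v 0.41: (1.96·√0.4998 + 0.8416·√0.4798)² / 0.04 = 96.9, giving 97.

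Both sizes reproduce and are used below.

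**2. Before-after effect size within one arm, identical masks.** Let d be the true mean change divided by the SD of the change, the same in both arms. Then d̂·√n follows a noncentral t distribution with n − 1 degrees of freedom and noncentrality d·√n. The probability of a label of medium or larger is P(T ≥ 0.2·√n), with 0.2·√63 = 1.59 and 0.2·√97 = 1.97. The last column pools the two patient groups (63 + 97 = 160), since the article does not say at which level effect sizes are computed.

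| Assumed shared change d | 63 per arm | 97 per arm | 160 per arm |
|---|---|---|---|
| 0 | 0.06 | 0.03 | 0.01 |
| 0.1 | 0.22 | 0.17 | 0.11 |
| 0.2 | 0.50 | 0.50 | 0.50 |
| 0.3 | 0.79 | 0.84 | 0.90 |
| 0.5 | 0.99 | 1.00 | 1.00 |
| 0.8 | 1.00 | 1.00 | 1.00 |

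The probability of a large label is 0.02 / 0.005 at d = 0.5, 0.51 / 0.51 at 0.8 and 0.92 / 0.96 at 1.0 (63 / 97 per arm).

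Dividing by the raw SD instead, in a simulation with pre-post correlation 0.3 to 0.7, gives at 0.3 SD 0.75 to 0.85 (63 per arm) and 0.80 to 0.89 (97 per arm). At 0.5 SD it gives 0.98 to 1.00 and 0.99 to 1.00.

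**3. Regression to the mean alone.** Simulated selection on PaO2/FiO2 ≤ 300, with no treatment effect, an assumed underlying mean of 200 to 300, SD 80 and correlation 0.5 to 0.9, gives a before-after d between 0.02 and 0.51. It can be negligible or can by itself pass 0.2, depending on inputs the article does not give.

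**4. Between-arm effect size after NIV, no mask difference.** d̂ = t·√(2/n), with 2n − 2 degrees of freedom.
- 63 per arm: 0.2 / √(2/63) = 1.12, so P(|d̂| ≥ 0.2) = 0.264.
- 97 per arm: 0.2 / √(2/97) = 1.39, so P(|d̂| ≥ 0.2) = 0.165.
- 160 per arm: 0.075.

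In the Owner mask's favour alone these are 0.13, 0.08 and 0.04. A large label by chance has probability below 0.0001.

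**5. What baseline adjustment gains.** Adjusting for a pre-NIV value with correlation ρ multiplies the residual variance by about 1 − ρ². At ρ = 0.5 this is 1 − 0.25 = 0.75; at ρ = 0.7 it is 1 − 0.49 = 0.51.

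**The case against.** **Within-arm is inferred.** Neither section says so. If the reference to the groups is taken to govern both halves of the sentence, the first effect size is a between-arm difference in change and the complaint about it falls. This stands as a caveat. The wording must then say so, and the sentence still needs correcting.

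**A between-arm effect size is already planned.** True. A reader might infer that the plan grades only before-after change; the same sentence shows otherwise. That second quantity is free of the shared NIV effect, though it is not adjusted for baseline.

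**No decision rests on the labels.** Also true. The arms are compared by GEE, chi-squared and Mann-Whitney tests, and nowhere is a label a success criterion. A reader might infer that the plan builds in a bias towards the Owner mask. It does not: with identical masks the control arm has the same expected effect size.

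**Could the labels differ between identical arms?** For two independent arms, the probability of different labels is one minus the sum of squared label probabilities. On a cut-off (0.2 or 0.8 SD) it is about 2 × 0.5 × 0.5 = 50%. At 0.3 SD it is 2 × 0.786 × 0.214 = 34% (63 per arm) or 2 × 0.837 × 0.163 = 27% (97 per arm). At 0.5 SD it is 1 − (0.971² + 0.009² + 0.020²) = 6%, or 1 − (0.993² + 0.002² + 0.005²) = 1%. The 50% figure therefore holds only at the cut-offs.

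**A size label is not a significance test, and intervals may be in a fuller document.** Both are fair. The chance rates in step 4 do not make 0.2 a wrong cut-off. They show only that the label says little without an interval. The article's silence on intervals is not itself counted as an error.

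**Conclusion.** The point holds in a limited form. On the natural reading, one of the two effect sizes cannot separate the mask from NIV, concomitant care and regression to the mean; the other separates them but discards the pre-NIV value.

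The size depends on the assumed shared change. A reader might infer that a medium label is the usual result with identical masks. That needs a shared change above 0.2 SD, which the documents do not establish: at 0.1 SD the figure is only 17 to 22% at the planned arm sizes. A large label becomes usual only above about 0.8 SD.

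The consequence is confined to effect sizes of continuous secondary outcomes. The primary outcome, "OTI rate in patients with or without suspicion or confirmation of SARS-CoV-2 infection submitted to NIV with Owner mask or conventional orofacial mask", is binary and has no value before NIV. Its comparison, the sample size and the planned between-group tests are untouched.

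**What to change.** In {20a} and {20b}, replace the two effect-size calculations with one rule:

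- For each continuous outcome with a pre-NIV value, report the between-arm difference at the stated time, adjusted for that value, in original units with a 95% confidence interval. Standardise by the baseline SD if wanted.
- Attach any small, medium or large label only to that between-arm estimate, beside its interval.
- State that within-arm changes are descriptive and are not evidence about the mask.

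The cost is new wording in two paragraphs. The data are already to be collected and the software is unchanged. What is lost is a before-after label that could be quoted for one arm alone.

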#### Interim analyses {21b}

DSMB recommendations will be notified directly to the research coordinator who will communicate to all parties involved in the research. The DSMB will carry out statistical analysis at a frequency to be established by the committee to detect the need to discontinue the study because of the primary outcome or due to the risk of occurrence of serious adverse outcomes, as well as ongoing assessment of the safety and relevance of the study design. The primary outcome of the study will be considered: OTI rate in patients with or without suspicion or confirmation of SARS-CoV-2 infection submitted to NIV with an Owner mask or with a conventional orofacial mask.

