#### Composition of the data monitoring committee, its role and reporting structure {21a}

The independent DSMB in this study is responsible for reviewing the reports regarding the safety of the study patients and protocol adherence and making recommendations to continue or terminate the study or modify sample size on the basis of the results from the interim analysis. The DSMB members are all independent of the sponsor and have no financial or other conflicts of interest.

The coordinator responsible for the study will send monthly reports containing the clinical efficacy and safety data collected during the study, which will be presented in spreadsheets, reports, and documents and will be forwarded to the members of the DSMB. Patients will be coded by numbers for blind analysis. All DSMB recommendations will be notified directly to the research coordinator who will communicate it to all parties involved in the study. The meetings will be held bimonthly via teleconference and the agenda for each meeting will be based on the discussions and recommendations generated in the previous meetings and on the events that may have occurred between them.

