#### Frequency and plans for auditing trial conduct {23}

The frequency of statistical analysis by the DSMB will be defined by this committee to ensure the safety and well-being of the research participants and the validity of the results obtained, as well as to monitor the occurrence of risks and benefits and detect evidence of achieving the primary objective of the research.

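### The DSMB may stop for the primary outcome and resize the trial on interim results at an open number of looks, and nothing in the plan protects the two-sided 0.05 level

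*Protocol article*

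**What the plan says.** All references are to the protocol article.

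- **Interim analyses {21b}**: the DSMB carries out "statistical analysis at a frequency to be established by the committee to detect the need to discontinue the study because of the primary outcome". Serious adverse outcomes are listed as a further reason to stop. Adverse event reporting and harms {22} repeats the provision.
- **Frequency and plans for auditing trial conduct {23}**: the committee sets how often it analyses, and one purpose is to "detect evidence of achieving the primary objective of the research". Objectives {7} defines the primary objective as a reduction in the risk of intubation with the Owner mask, so these looks include efficacy.
- **Composition of the data monitoring committee {21a}**: the committee may recommend continuing, ending, or to "modify sample size on the basis of the results from the interim analysis". Efficacy and safety reports go to it monthly and it meets bimonthly. The section also says that patients are number-coded so that the analysis is blind.
- **Sample size {14}**: each population is sized "with the adoption of a two-tailed model and a significance level of 0.05".
- **Statistical methods {20a} and additional analyses {20b}**: both keep p < 0.05. The only multiplicity adjustment named is a Bonferroni post hoc test attached to the GEE model, which does not concern interim looks.

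**The concern.** A two-sided 0.05 test has a 5% error rate when it is done once, on a sample size fixed in advance. This plan allows repeated comparison of intubation rates, with the option to end the trial on what is seen, and allows the sample size to change in response to interim results. Either permission can raise the chance of a false claim of benefit unless a rule set in advance limits it.

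This goes beyond detail that an article leaves out. The article states the permissions, hands the number of looks to the committee, and fixes the only significance level it mentions at the single-look value. Intubation is the sole primary outcome. If the trial stopped early or was resized under these provisions, the p-value for its main result could not be interpreted at face value.

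**Working it through.** **1. Is any alpha held back for interim looks in the sample size?**

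Inputs from Sample size {14}: COVID-19 population "based on an OIT rate of 30.2% for patients with COVID-19 who require mechanical ventilation" and "80% of power to detect an absolute reduction of 20% of the primary result"; other population "Assuming an intubation rate of 61% for patients with acute respiratory syndrome requiring mechanical ventilation" and "80% power to detect an absolute reduction 20% of the primary result"; two-sided 0.05. Allocation is 1:1 (Trial design {8}).

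Formula (pooled variance, no continuity correction), with p̄ the mean of p1 and p2:

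n per group = [1.960·√(2p̄(1−p̄)) + 0.842·√(p1(1−p1) + p2(1−p2))]² / (p1−p2)²

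- COVID-19, 30.2% to 10.2%: (1.113 + 0.463)² / 0.04 = 62.1, so **63**. Stated: 63.
- Non-COVID-19, 61% to 41%: (1.386 + 0.583)² / 0.04 = 96.9, so **97**. Stated: 97.

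Both match, with power of 80.6% and 80.0%. Continuity-corrected (72 and 107), one-sided (49 and 77), unpooled (60 and 95) and arcsine (60 and 97) versions do not reproduce both figures. The stated sizes are therefore single-look designs that use the full 0.05.

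**2. What would repeated looks at 0.05 do?**

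The article gives neither the number of looks nor a threshold, so both are assumptions here. Model: K equally spaced looks including the final one, Z_k = S_k/√k, with S_k a sum of k independent standard normals and no true effect. Reject if |Z_k| > 1.96 at any look. One million simulated paths were used, plus 200,000 simulated binary trials per case at the plan's own control rates and group sizes.

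| Looks | Overall error, normal model | Binary, 30.2%, 63 per group | Binary, 61%, 97 per group |
|---|---|---|---|
| 1 | 5.0% | 5.1% | 4.9% |
| 2 | 8.3% | 8.6% | 8.2% |
| 3 | 10.8% | 11.3% | 11.3% |
| 5 | 14.2% | 14.9% | 14.9% |
| 10 | 19.4% | 21.6% | 18.9% |

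Ten looks is the upper-end case. Trial status gives 1 September 2020 to 30 April 2022, which is 20 months. Taking bimonthly as every two months, 20 / 2 = 10 meetings, each assumed to include an efficacy test.

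**3. What would hold the error at 5%?**

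- Constant boundary: nominal p of about 0.029 (2 looks), 0.022 (3), 0.016 (5) or 0.011 (10) at every look.
- O'Brien-Fleming boundary: final p of about 0.048, 0.045, 0.041 or 0.037.
- Haybittle-Peto (p < 0.001 at each interim, final test at 0.05): simulated overall error between 5.0% and 5.2% for up to 10 looks.

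Power was simulated in the same model for a design with 80% power at one look (mean of the final Z = 1.960 + 0.842 = 2.802). Haybittle-Peto keeps 80%. O'Brien-Fleming gives 79.7%, 79.2%, 78.8% and 78.3% for 2, 3, 5 and 10 looks.

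**4. Sample-size change.**

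The article states no method, so only a ceiling can be given. With one interim, a second-stage size chosen from the unblinded result to do the most damage, and an unadjusted final test, the one-sided error is 0.025 + exp(−1.96²/2)/4 = 0.025 + 0.037 = 0.062. A change based on pooled data blind to arm would barely move it.

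**The case against.** The strongest reply is that no section says interim data will be tested at 0.05. The 0.05 belongs to the sample size and the general analysis, and a boundary commonly sits in a DSMB charter or SAP, neither of which is shown. A final test at 0.05 is also compatible with interim looks: Haybittle-Peto leaves the Sample size and Statistical methods sections as they are. This stands, and it rules out saying that the error rate *is* above 5%. It does not remove the point, because the article itself grants the permissions without making them subject to any error-controlling rule.

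Three stronger readings are tempting and are not supported.

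- *Ten efficacy tests are planned.* Meetings are not efficacy analyses. {21a} ties meeting agendas to earlier discussions and events, {21b} leaves analysis frequency as a separate decision, and {21a} speaks of the interim analysis in the singular. A stop on the primary outcome could also be for harm or futility, which does not inflate a benefit claim.
- *The sample size will follow the observed difference between arms.* {21a} does not say so, and it mentions coded, blind analysis. That wording weighs against the reading but does not settle it: coding patients by number does not confine resizing to the pooled rate, and a committee looking for evidence that the primary objective is met has to compare arms.
- *Sizing the COVID-19 and non-COVID-19 populations each at 0.05 adds a familywise error.* No section says that success in either population alone would make the trial positive, and whether claims in separate populations need joint control is debated. It is no part of this point.

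**Conclusion.** The point holds in this form: the plan as written does not control the 5% type I error for the primary outcome. That follows from the text alone, from open-ended looks that include efficacy, permission to stop on them, permission to resize on interim results, and a single-look 0.05.

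The size of the inflation does not follow from the text. The range of about 8% to 19% for 2 to 10 looks assumes equal spacing, a test at 0.05 each time, and that any look could end in a claim. With strict boundaries it would be close to 5%. The 0.062 ceiling for resizing is a worst case, not a forecast.

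**What to change.** 1. In {21b}, with matching text in {22} and {23}, state that any stop for efficacy follows a boundary fixed in advance. Either Haybittle-Peto (p < 0.001 at each interim, final test at 0.05), or O'Brien-Fleming-type alpha spending, serves. Alpha spending lets the committee keep flexible look times, provided that they are not chosen from the observed effect. Say separately that reviews for harm or futility cannot lead to a claim of benefit.
2. In {21a}, replace the wording that lets interim results drive the sample size. Limit any change to the pooled intubation rate, blind to arm, by a stated method.
3. Recruitment began before protocol version 1.0 was dated, so report any comparison of arms already seen by the committee and count it as a look.

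Cost: amended wording in the protocol and DSMB charter. An efficacy stop would need stronger evidence. Haybittle-Peto costs no power. O'Brien-Fleming costs 0.3 to 1.7 points from 80% for 2 to 10 looks (80 − 79.7; 80 − 78.3), so the planned sizes need not change.
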